#### 12- to 24-Week Period

Following the completion of the 12-week online survey, participants in the intervention group will enter a maintenance phase and will not receive further chatbot interactions. In addition, they will receive weekly SMS text message reminders reinforcing key heart attack knowledge and prompting completion of the final online survey at week 24. The waitlist control group will begin the HeartBot II intervention, following the same 4 modules schedule as the intervention group starting at week 12. They will receive the same instructions and reminders throughout the 12- to 24-week period. At week 24, all participants will complete the final online survey. For the intervention group, this represents a follow-up assessment three months postintervention; for the waitlist control group, it represents the follow-up assessment 3 weeks postintervention. If all participants complete all study requirements, they will receive a US $20 Amazon e-gift card. To minimize the burden on participants’ time, all study procedures will be done online remotely. Data collected during the surveys will be captured on the REDCap system.

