#### Statistical Analysis

Baseline characteristics will be summarized by randomized group using counts and percentages for categorical variables and means and standard deviations for continuous variables, or medians and interquartile ranges for skewed variables. Because treatment assignment is randomized, baseline characteristics will be described primarily to assess sample comparability rather than to guide significance-based inference.

Primary efficacy analyses will compare randomized groups from baseline to 12 weeks, before the waitlist group receives the intervention. The treatment effect for the primary outcome, a 4-item heart attack response preparedness score, will be estimated using constrained longitudinal data analysis (cLDA) implemented via linear mixed models (LMMs) [37]. Consistent with the randomized design, the models will constrain the mean scores for the treatment and control groups to be equal at baseline. The primary outcome will include categorical fixed effects for time and a time-by-treatment group interaction term. The primary model contrast of interest is the coefficient for this interaction term at the 12-week follow-up, representing the baseline-adjusted between-group difference. To account for the within-subject correlation between baseline and follow-up, the cLDA models will use an unstructured covariance matrix, allowing variances and correlations to differ over time.

The 4 individual preparedness items will be analyzed as prespecified key secondary outcomes, subject to the hierarchical gatekeeping procedure described above. The primary efficacy analysis and all key secondary analyses will be based on the baseline and 12-week assessments only. Although the individual items are ordinal, the primary analysis will use the same linear cLDA framework to facilitate interpretation of mean differences and support model stability [38]. Robustness of this linear approximation will be evaluated in sensitivity analysis using ordinal logistic mixed-effects models for each individual item.

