Exploratory analysis of the 24-week assessment will evaluate the maintenance effects among participants originally randomized to HeartBot II and within-group changes after they receive the intervention. Because the waitlist control group receives the intervention after week 12, 24-week between-group comparisons also lack randomized control protection. Therefore, exploratory analysis of all available repeated measurements (baseline, 12 wk, and 24 wk) will be conducted using an unconstrained linear mixed model with a participant-specific random intercept and fixed effects for treatment group, timepoint, and their interaction. Because treatment exposure is no longer randomized after week 12, these analyses will be considered exploratory and descriptive rather than confirmatory.

Exploratory secondary outcomes will be analyzed using methods appropriate to their scale and distribution. Continuous secondary outcomes will be analyzed using linear regression or linear mixed models, as appropriate to the timing of measurement. Binary or categorical secondary outcomes will be analyzed using generalized linear models or generalized linear mixed models.

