#### Power and Sample Size

This study is powered based on a total analyzed sample of n=160 (80 per group). To account for a conservative 20% attrition, we will enroll a total of 200 participants. Statistical power was estimated via Monte Carlo simulations (5000 iterations) using an empirical covariance matrix and response thresholds derived from pilot data [18]; code is provided in Multimedia Appendix 1. The simulation uses the same cLDA analysis framework described above for analysis.

For the primary outcome, the heart attack response preparedness score, the study provides 90% power to detect a raw mean difference of 0.37 points on the 1‐4 scale (Cohen *d*=0.51). This detectable effect is smaller than the within-group mean change observed in pilot data (0.78 points), although the pilot study did not include a control group [18]. For the four key secondary item-level outcomes, power was also evaluated under the prescribed hierarchical gatekeeping procedure with Holm-Bonferroni adjustment. Under this framework, the study has 90% power to detect at least one significant key secondary item for a raw difference of 0.43 (*d*=0.59). To detect significant effects across all four key secondary items (assumed to have the same effect), larger effect sizes are required; 90% power is achieved at a mean difference of 0.62 points (*d*=0.85).

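### The exploratory 24-week model has only a random intercept, so its within-arm intervals are calibrated only if variances and correlations are equal across visits and arms

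*Protocol article*

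**What the plan says.** The Statistical Analysis section uses two covariance specifications.

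- **Baseline and week 12.** "The primary efficacy analysis and all key secondary analyses will be based on the baseline and 12-week assessments only". For this analysis "the cLDA models will use an unstructured covariance matrix, allowing variances and correlations to differ over time".
- **Baseline, week 12 and week 24.** The plan is an "exploratory analysis of all available repeated measurements (baseline, 12 wk, and 24 wk"), fitted with an "unconstrained linear mixed model with a participant-specific random intercept and fixed effects for treatment group, timepoint, and their interaction". No residual structure, arm-specific covariance or robust standard error is named.

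The purpose of the 24-week analysis is that it "will evaluate the maintenance effects among participants originally randomized to HeartBot II and within-group changes after they receive the intervention". The reason given for changing model is that exposure is no longer randomized after week 12, and "these analyses will be considered exploratory and descriptive rather than confirmatory".

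On the design, the section on the 12- to 24-week period says: "The waitlist control group will begin the HeartBot II intervention, following the same 4 modules schedule as the intervention group starting at week 12".

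**The concern.** A random intercept with constant residual variance is a compound-symmetry model: every visit has the same variance and every pair of visits the same correlation, in both arms. The crossover makes that doubtful. The week 12 and week 24 visits are a post/post pair in the HeartBot II arm and a pre/post pair in the waitlist arm. With equal numbers per arm, the model still gives both arms the same standard error for the 12-to-24-week change.

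The stated reason, loss of randomized exposure, explains dropping the equal-baseline constraint. It does not bear on the covariance.

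What is at stake is the width of the intervals around the within-arm changes that this analysis is meant to describe. Too wide an interval in the HeartBot II arm could let a real decline pass as maintenance. Too narrow an interval in the waitlist arm would make the gain there look more precise than it is.

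**Working it through.** **Inputs from the protocol (Power and Sample Size).** The plan assumes a "total analyzed sample of n=160 (80 per group"), 90% power, and a difference of 0.37 points with d = 0.51. The implied SD is 0.37/0.51 = 0.725.

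**The plan's own figure.** A two-sample comparison with 80 per arm, difference 0.37, SD 0.725 and two-sided alpha 0.05 has power 89.7%, against 90% stated. Enrolment is 160/(1 − 0.20) = 200. Both reproduce. No figure is stated for the 24-week model.

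**Assumed inputs.** The protocol gives no correlation between visits. The values below are assumptions: one correlation for same-state pairs (pre/pre and post/post), another for pre/post pairs, and equal variances unless stated. The SD cancels from the ratios.

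**Formulas (complete data, n = 80 per arm).**

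- True SE of a within-arm change: SD × √(2(1 − ρ)/n), with ρ the correlation of that pair in that arm.
- Random-intercept SE: the same expression with the average of all pairwise correlations. Each arm has one same-state pair and two pre/post pairs, so the average is (same + 2 × pre/post)/3.
- Coverage of a nominal 95% interval: 2Φ(1.96 × ratio) − 1, where ratio = model SE/true SE.

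**Worked case, 0.6 against 0.3.** The average correlation is (0.6 + 0.3 + 0.3)/3 = 0.4. The HeartBot II ratio is √(1.2/0.8) = 1.22 and the waitlist ratio is √(1.2/1.4) = 0.93.

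**SE of the 12-to-24-week change.**

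| Same-state / pre-post correlation | Model SE, both arms | True SE, HeartBot II (ratio; coverage) | True SE, waitlist (ratio; coverage) |
|---|---|---|---|
| 0.5 / 0.5 | 0.0811 | 0.0811 (1.00; 95.0%) | 0.0811 (1.00; 95.0%) |
| 0.6 / 0.5 | 0.0784 | 0.0725 (1.08; 96.6%) | 0.0811 (0.97; 94.2%) |
| 0.6 / 0.4 | 0.0838 | 0.0725 (1.15; 97.6%) | 0.0889 (0.94; 93.5%) |
| 0.6 / 0.3 | 0.0889 | 0.0725 (1.22; 98.4%) | 0.0960 (0.93; 93.0%) |
| 0.7 / 0.3 | 0.0864 | 0.0628 (1.37; 99.3%) | 0.0960 (0.90; 92.2%) |

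Mixed-model fits to 150 simulated trials in each of three scenarios (0.5/0.5, 0.6/0.4, 0.7/0.3) gave model SEs of 0.0807, 0.0840 and 0.0861 in both arms, in line with the closed form.

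**In points on the scale.** At 0.6/0.3, the decline in the HeartBot II arm needed to reach p < 0.05 is 1.96 × 0.0725 = 0.14 with the true SE and 1.96 × 0.0889 = 0.17 with the model SE.

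**Unequal variances.** With all correlations 0.5 but the post-intervention SD 0.8 times the pre-intervention SD, the HeartBot II SE is 0.0740 against a true 0.0649 (14% too large). The waitlist SE is about right (0.0740 against 0.0743).

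**Would a shared unstructured matrix cure it?** It averages the 12/24 correlation over the arms. At 0.6/0.3 that is 0.45, giving ratios √(1.1/0.8) = 1.17 and √(1.1/1.4) = 0.89. At 0.7/0.3 it is 0.5, giving 1.29 and 0.85. In these scenarios the HeartBot II error shrinks a little and the waitlist error grows.

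**The case against.** The strongest reply is that nothing in the protocol shows the covariance departs from compound symmetry. That stands. The correlations are assumed, every unequal case in the table has same-state pairs correlating more than pre/post pairs, and equality gives no error. A reader might infer that the standard errors are simply wrong; the documents support only that they are wrong unless equality holds.

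The direction is also less certain than the table suggests:

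- In weeks 12 to 24 the HeartBot II arm gets weekly messages reinforcing heart attack knowledge, so its week 12 and week 24 visits are not clearly under one unchanged state.
- If pre/pre visits correlate 0.7 and all other pairs 0.5, the SE is 3% too small in both arms.
- Maintenance is not defined as the 12-to-24-week change. Read as baseline to week 24 in the HeartBot II arm, it is a pre/post contrast, and at 0.6/0.3 its SE is 7% too small.

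A reader might also infer that keeping the primary model's unstructured matrix would solve the problem. The working shows that it would not unless the matrix differs by arm. Nor does the primary model's rationale anticipate this issue: it concerns correlation between baseline and one follow-up.

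Finally, the analysis is labelled exploratory, and an article may leave residual structure or the type of standard error to a fuller plan. That lowers the priority. But the random intercept is a stated choice, and in a descriptive analysis the estimate and its interval are the result.

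**Conclusion.** The point holds conditionally and is minor. As written, the 24-week model gives calibrated within-arm intervals only if variances and correlations are equal across visits and arms, which the crossover makes doubtful and the protocol does not address. Over the assumed range of 0.6/0.5 to 0.7/0.3, nominal 95% coverage for the 12-to-24-week change runs from about 97% to 99% in the HeartBot II arm and from 94% down to 92% in the waitlist arm. This rests on assumed correlations, equal variances, complete data with 80 per arm, and constant residual variance.

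With complete data the point estimates are the arm-by-visit means and do not change. The primary and key secondary analyses use baseline and week 12 only, so a reader should not infer any effect on them or on the power statement.

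**What to change.** Make one of two changes to the week 0/12/24 model:

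1. Fit an unstructured 3x3 covariance estimated separately by randomized arm and take the within-arm contrasts from it. This needs 6 covariance parameters per arm, from about 80 women in each.
2. Keep the random intercept and report robust (sandwich) standard errors clustered on participant.

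Either calibrates the intervals whatever the true correlations are. The model can stay unconstrained at baseline, as planned. It would also help to state which visit-to-visit contrast is meant by maintenance and which arm each within-group change refers to.

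The cost is a line of analysis code and a sentence in the plan, with no new data. Recruitment began in April 2026 and was still open on June 2, 2026, so no week-24 data could then exist and the change could be made before any were seen.

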#### Randomization

200 women will be randomly assigned in a 1:1 ratio to the HeartBot II intervention or a waitlist control group. Permuted-blocked randomization will be used to ensure balance between groups, with block sizes varying randomly among 2, 4, and 6. The randomization scheme will be generated and implemented in REDCap by a staff member who is not involved in participant recruitment, intervention delivery, data collection, or outcome assessment. Investigators and research staff will be blinded to block size and allocation sequence. The individual preparing the randomization scheme has no role in evaluating or executing the experiment. Participants will be informed of their assignment after randomization.

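### The week-12 crossover removes the untreated comparator, not the randomisation, so it is no reason to drop the equal-baseline constraint from the 24-week model

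*Protocol article*

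**What the plan says.** All references are to the Methods of the protocol article.

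- **Randomization:** "200 women will be randomly assigned in a 1:1 ratio to the HeartBot II intervention or a waitlist control group". The Baseline section places the baseline survey before this step.
- **Statistical Analysis, primary model:** "Consistent with the randomized design, the models will constrain the mean scores for the treatment and control groups to be equal at baseline". The model uses the baseline and week-12 visits with an unstructured covariance.
- **12- to 24-Week Period, waitlist arm:** "The waitlist control group will begin the HeartBot II intervention, following the same 4 modules schedule as the intervention group starting at week 12".
- **12- to 24-Week Period, intervention arm:** no further chatbot sessions, but "they will receive weekly SMS text message reminders reinforcing key heart attack knowledge".
- **Same section, timing of the week-24 survey:** "For the intervention group, this represents a follow-up assessment three months postintervention". The matching statement about the delayed-start arm reads: "for the waitlist control group, it represents the follow-up assessment 3 weeks postintervention".
- **Statistical Analysis, 24-week analysis:** because the waitlist arm has by then been treated, "24-week between-group comparisons also lack randomized control protection". As a stated consequence, the three visits are to be analysed with an unconstrained linear mixed model with a random intercept and terms for group, time and their interaction. The section closes: "Because treatment exposure is no longer randomized after week 12, these analyses will be considered exploratory and descriptive rather than confirmatory".

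**The concern.** The primary model's equal-baseline constraint is justified by randomisation. The 24-week model drops it because of something that happens at week 12. A week-12 event cannot alter the distribution of a variable measured before allocation, so the stated reason does not support the modelling choice.

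The same section also drops the constraint for the per-protocol and dose-response analyses. There the reason is sound, because module completion is self-selected. The 24-week analysis involves no such selection: nobody is re-allocated, nobody chooses a start time, and the section says all analyses keep participants in their assigned groups.

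Two things are at stake. Without the constraint, chance baseline imbalance enters the week-12 and week-24 group-by-time terms and widens their intervals for no benefit. And the wording may lead readers to treat the week-24 between-arm contrast as a comparison of non-randomised groups, when what has changed is the question it answers.

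**Working it through.** **1. What is randomised at week 24.** On the module schedule, Module 4 opens at week 9 in the intervention arm and at 12 + 9 = week 21 in the waitlist arm. At week 24 it has therefore been open for 24 − 9 = 15 weeks in one arm and 24 − 21 = 3 weeks in the other. Both schedules follow from the single 1:1 allocation. The contrast is a randomised comparison of two strategies: immediate start plus reinforcing messages, and delayed start.

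**2. Inputs.** From Power and Sample Size: 80 analysed per arm, and 0.37 points corresponding to d = 0.51, so SD = 0.37/0.51 = 0.725. Assumed: the same variance at each visit, 80 per arm at week 24, and a correlation r between any two visits, as a random intercept implies. The pilot covariance matrix is cited but not printed in the article, so r is shown over a range.

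**3. The plan's own figure.** For 80 per arm and two-sided alpha 0.05, 0.51/√(2/80) = 3.23; 3.23 − 1.96 = 1.27, giving power 0.897 (0.894 with the noncentral t). The stated 90% is reproduced, and 160/(1 − 0.20) = 200. This fixes the scale but not r, because the article does not say which standard deviation d refers to. The percentage losses below do not depend on the SD.

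**4. Standard error of the week-24 group-by-time contrast.**

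- Constrained: variance = 2·SD²·(1 − r²)/n
- Unconstrained (difference in change from baseline): variance = 4·SD²·(1 − r)/n
- Variance ratio = 2/(1 + r)

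| r | Constrained SE | Unconstrained SE | Variance ratio | SE increase |
|---|---|---|---|---|
| 0.2 | 0.112 | 0.145 | 1.67 | 29% |
| 0.3 | 0.109 | 0.136 | 1.54 | 24% |
| 0.5 | 0.099 | 0.115 | 1.33 | 15% |
| 0.7 | 0.082 | 0.089 | 1.18 | 8% |
| 0.8 | 0.069 | 0.073 | 1.11 | 5% |

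At r = 0.5, the difference detectable with 90% power is (1.96 + 1.28) × SE: 0.32 constrained and 0.37 unconstrained. Under the same assumptions the week-12 interaction in this three-visit model loses the same proportion. If the week-24 difference in level is read off instead, the unconstrained SE is √(2·SD²/n) = 0.115, which is 2%, 15% or 67% larger than the constrained SE at r = 0.2, 0.5 or 0.8.

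**5. Validity of using the baseline this way.** In 10,000 simulated null trials at r = 0.5, the baseline-adjusted week-24 comparison of the arms had mean 0.0003, type I error 0.0498 and SE 0.100. The unadjusted difference in change had SE 0.115.

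**6. What does not change.** The within-arm change from week 12 to week 24 has SE √(2·SD²·(1 − r)/n) = 0.096, 0.081 and 0.063 at r = 0.3, 0.5 and 0.7, with or without the constraint. For a within-arm change from baseline to week 24 at r = 0.5, the SE is 0.076 with the constraint and 0.081 without it, about 7% larger.

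**The case against.** The strongest reply is that little is lost. The section's stated 24-week aims are maintenance in the HeartBot II arm and within-group change after treatment. Step 6 shows that the week-12-to-24 changes are estimated equally well either way. The planned model is unbiased, the analysis lies outside the gatekeeping procedure, and no confirmatory result depends on it. All of this stands and sets the severity. It does not supply a reason for dropping the constraint, and the chosen model does estimate group-by-time terms.

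A second reply concerns the wording. "24-week between-group comparisons also lack randomized control protection" follows directly from the waitlist arm being treated, and can be read as saying only that no randomised unexposed control remains, which is true. That also stands. A reader might infer that the article flatly denies the randomisation, but this phrase does not require that reading. The closing sentence on treatment exposure is looser and is the one to change. On either reading, the absence of an unexposed control says nothing about baseline means.

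A third reply is that week 24 is not a clean randomised test of persistence against recency. That is correct. The intervention arm receives reinforcing messages in weeks 12 to 24, so time since the modules and message reinforcement are mixed. The contrast can be read only as one strategy against another.

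**Conclusion.** The point holds as a minor one. The reason given does not justify removing the equal-baseline constraint, and removing it costs precision in the between-arm group-by-time contrasts: about 24%, 15% or 8% in SE at r = 0.3, 0.5 or 0.7. These figures assume equal variances and a common correlation. The absolute SEs also assume SD 0.725 and 80 per arm, a number the article gives for the powered analysis and not specifically for week 24. Since r is not given, the size of the loss is uncertain.

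A reader might infer more: that the 24-week analysis is biased, that all its results are imprecise, or that it should become confirmatory. The document supports none of these. The unconstrained model is valid, the loss does not reach the week-12-to-24 within-arm changes under the random-intercept structure, and the exploratory label is right because the analysis is outside the gatekeeping and no unexposed control remains. The primary week-12 analysis and its power are unaffected.

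**What to change.** In the 24-week paragraph of Statistical Analysis:

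1. Fit the baseline, week-12 and week-24 model with the equal-baseline constraint and an unstructured covariance over the three visits, in line with the primary model. Restoring the constraint alone would leave the random-intercept covariance, so the week-12 estimate from this model could still differ from the primary one for technical reasons.
2. Replace the sentence saying that exposure is no longer randomised with a statement to this effect: at week 24 the arms remain randomised to immediate versus delayed HeartBot II, including their follow-up messages; no unexposed control remains, so the contrast does not estimate HeartBot II versus none.
3. Keep the analysis exploratory, and reserve the caution about non-randomised comparison for within-arm changes.

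The cost is a few sentences and one model specification, settled before analysis begins in spring 2027. It needs no new data and does not affect participants.
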